### Criteria for discontinuing or modifying allocated interventions {11b}

If clinical deterioration, an adverse event (AE) or a serious adverse event (SAE) is detected throughout the course of the trial by an outcome assessor or facilitator, it will be promptly reported to the research team, trial sponsor, ethics committees and Data Safety and Management Board (DSMB), see Sect. 22 for further details. Where an AE or SAE occurs, participants will be referred to specialist support if deemed necessary by the research director and research team using previously developed remote referral pathways. Clinical deterioration includes instances where a participant is intoxicated during multiple sessions, reports suicidal ideation, or homicidal ideation. Participants who report suicidal ideation will only be referred to specialist services or withdrawn from the trial if they are at imminent risk of suicide, which involves having a plan in place. Participants referred to specialist support during baseline outcome assessment or the CHANGE intervention sessions will be withdrawn from the trial but may continue to receive the remaining CHANGE sessions. If participants are referred to specialist support at the 3-month outcome assessment, they will not be withdrawn from the trial. All facilitators and outcome assessors have received training in safety protocols for remote service delivery and to ensure adherence to best practice.

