### Provisions for Posttrial care {30}

The 14 facilitators trained to deliver the CHANGE intervention in Ukraine will continue their work and provide care to the community after the trial concludes. Additionally, CETA, which is implemented by the community-based NGO WordsHelp will be available for participants who need additional care. CETA is a treatment program for adults presenting with transdiagnostic problems (e.g. PTSD, depression, anxiety and substance use) developed specifically for use with community workers in low- and middle-income countries and has been proven effective in the context of Ukraine [29]. Participants may be referred to or choose to self-refer to these services. Where participants access CETA during the trial they will be excluded from the analysis.

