### Sample size {14}

A sample size of 500 enrolled participants (250 in each arm with 1:1 allocation) will provide 90% power (alpha = 0.05) to detect a difference in participants’ PDA from alcohol at follow-up of 55% in the EUC arm vs 68% in the CHANGE arm. This assumes participants’ PDA from alcohol is distributed with a standard deviation of 37% in both arms [37]. Both the effect size and the standard deviation are based on the Counselling for Alcohol Problems (CAP) trial (54% vs. 69%). The sample size calculation accounts for 20% loss to follow-up at 3 months and is based on Nadkarni et al. 2017 [37].

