## Statistical methods

### Statistical methods for primary and secondary outcomes {20a}

In line with the protocol published by van der Boor et al. [23], a statistical analysis plan will be written by the statistician based at the London School of Hygiene and Tropical Medicine and approved by the Data Safety and Management Board (DSMB) prior to unmasking of the data and analysis. The quantitative data will be analysed using Stata 17.0. An initial analysis will be conducted to compare participants who did and did not provide consent for participation following initial screening. Further descriptive analysis will then be carried out to compare the baseline characteristics of the participants. If substantial baseline imbalances exist in characteristics that are likely to affect outcomes, these will be adjusted a priori to the outcome analyses.

Binary outcomes will be analysed using logistic regression or negative binomial regression, depending on the distribution. Marginal standardization and delta methods [38] will be used to calculate adjusted risk ratios if logistic regression is used. Continuous outcomes will be analysed using linear regression, and adjusted mean differences reported. Before analysis, distributions of all outcome variables will be inspected, and if necessary, transformations or other modelling options will be considered.

All models will be adjusted for baseline characteristics that differ between the arms as determined by the descriptive analysis and the baseline measures. *P* values will not be used to identify differences between arms at baseline, as these are assumed to be at random. Fully adjusted (if appropriate) model results will be presented and reported using CONSORT guidelines [39]. Intention to treat principles will be used for the primary analysis.

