A critical incident register will be maintained during the study to record specific SAEs and AEs. An overview of the types of SAEs and AES can be found in Table 5. SAEs and AEs that are detected during any of the outcome assessments or intervention sessions will be disclosed immediately to the local research director and site PI who will become unmasked. For each individual event, a report will be written. Based on the type of event, the participant will be asked to give consent for further evaluation, assessment, and/or follow-up by a designated health professional (see Table 6). If the participant experiencing an AE or SAE was in the intervention arm of the trial, and once they are referred to further care their data will be excluded from the analysis. Nonetheless, if they are able to, they can receive further CHANGE sessions. The exception to this is referrals for intimate partner violence, whereby participants will be encouraged to access protection services, but will not be excluded from the analysis.

**Table 5 Tab5:** Expected and unexpected SAE and AEs (adapted from Van Der Boor et al., 2024 [23])

	Expected	Unexpected
SAE	Victimization (violence against the trial participant or nuclear family)	Death of the trial participant due to suicide
	IPV (violence against family members by participant, or violence against participant by family member)	Death of the trial participant due to other causes
	Suicide attempt	Hospital admission of trial participant due to a psychiatric problem
	Homicidal ideation	Planning and/or going through with the homicidal ideation
	Stigmatisation	Hospital admission of trial participant due to other causes (i.e. serious medical emergency)
	Serious lack of food / Critically unsatisfied basic needs	
AE	Clinical deterioration of the participant	
	Emotional distress caused by a trial procedure (either by the outcome assessment or the intervention delivery)

**Table 6 Tab6:** SAE referral according to intervention arm

SAE	Reported at outcome evaluation in both arms, referral to:	Reported by facilitator in the intervention arm only, referral to:
Hospital admission of participant due to serious medical emergency^a^	General physician (GP), family doctor	GP, family doctor
Hospital admission of participant due to a psychiatric problem	Independent psychiatrist, Psychiatrist in the hospital	Independent psychiatrist, Psychiatrist in the hospital

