Victimisation (violence against the participant)	Independent psychologist, social worker, humanitarian agency representative	Intervention supervisor
Severe IPV perpetrated by participant (violence against family members by participant) that includes a risk of severe injury and/or death	Independent psychologist, social worker, humanitarian agency representative	Intervention supervisor
Suicide attempt	Independent psychiatrist, Psychiatrist in the hospital	Independent psychiatrist, Psychiatrist in the hospital
Homicidal ideation	Independent psychiatrist, Psychiatrist in the hospital	Independent psychiatrist, Psychiatrist in the hospital
Stigmatization^a^	Intervention supervisor	Intervention supervisor
Death of the trial participant	N/A	N/A
Any violence toward others	Independent psychiatrist, social worker, humanitarian agency representative	Independent psychiatrist,
Serious lack of food/ Critically unsatisfied basic needs	GP, primary health care worker (nurse/ midwife)	GP
**AE**		
Clinical deterioration of trial participant, including a high risk of a suicide attempt	Independent psychiatrist, Psychiatrist in the hospital	Independent psychiatrist, Psychiatrist in the hospital
Emotional distress caused by a trial procedure (either by the outcome assessments or the intervention delivery)	Independent psychologist, Psychiatrist in the hospital	Independent psychologist, Psychiatrist in the hospital

^a^Prior to referral to the nominated healthcare professional, these SAEs will have an independent clinician review the SAE narrative to determine if this is indeed a SAE

During the 3-month follow-up assessment, all participants will be asked to respond to the safety questions (related to suicide and homicidal ideation) again. In the case of an SAE detection, an independent psychiatrist will assess the participant, and the SAE report will be completed. Participants with safety issues identified during the follow-up will not be excluded from the trial. These questions aim to identify any problems and provide timely referral pathways.

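### Excluding referred CHANGE-arm men, and CETA users in either arm, contradicts the promised intention-to-treat analysis; the one-arm rule probably favours CHANGE

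*Protocol article*

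**What the plan says.** All references are to the protocol article.

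- **Principle.** Statistical methods {20a}: "Intention to treat principles will be used for the primary analysis". The abstract and the missing-data section {20c} repeat this.
- **AE/SAE rule.** Adverse event reporting {22}: the data of a man with an AE or SAE are dropped if he was "in the intervention arm of the trial, and once they are referred to further care their data will be excluded from the analysis". Referrals for intimate partner violence are exempt.
- **Withdrawal rule.** Criteria for discontinuing {11b}: "Participants referred to specialist support during baseline outcome assessment or the CHANGE intervention sessions will be withdrawn from the trial". Men referred at the 3-month assessment are not withdrawn.
- **What can trigger it.** {11b}: "Clinical deterioration includes instances where a participant is intoxicated during multiple sessions"; reported suicidal or homicidal ideation also counts. Table 5 lists clinical deterioration as an AE, and Table 6 directs it to a psychiatrist.
- **Events found at 3 months.** {22}: "Participants with safety issues identified during the follow-up will not be excluded from the trial".
- **CETA rule.** Post-trial care {30}: "Where participants access CETA during the trial they will be excluded from the analysis". This is not limited to one arm.
- **Outside care.** Concomitant care {11d} permits it and foresees recording referrals so that a sensitivity analysis can be run.

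No section confines these exclusions to a secondary or per-protocol analysis.

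**The concern.** An analysis plan cannot both keep all randomised men and discard some of them for what happens after randomisation. The AE/SAE rule is the more serious case because it names one arm only and its triggers are related to outcome. A man who drinks through his CHANGE sessions can be classed as deteriorating, referred and removed, while a comparable man in EUC stays in. The primary outcome is percentage of days abstinent (PDA), and the secondary outcomes include distress. Selective removal from CHANGE would therefore make that arm look better than it is. Adjustment for baseline covariates cannot restore men who were taken out because of later events.

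The CETA rule is a separate conflict. It covers both arms, and it contradicts the concomitant-care section as well as intention to treat.

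**Working it through.** **1. Is the AE/SAE rule really one-sided?** {22} names the intervention arm. After randomisation, the withdrawal rule in {11b} can act only through CHANGE sessions. EUC men receive one consultation ({6b}), and their next scheduled assessment is at 3 months, where flagged men are kept ({11b}, {22}). Referral at the baseline assessment comes before randomisation and causes no bias.

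**2. Do the sections agree with each other?** Not fully. The exclusion sentence in {22} follows one that covers events detected at any outcome assessment as well as at sessions. Read literally, it also excludes CHANGE men flagged at 3 months, whereas {11b} and the later text of {22} keep such men in the trial.

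**3. The plan's own figure.** Inputs from Sample size {14}: 250 per arm, 20% loss (leaving 200 per arm), 55% vs 68% PDA (13 points), SD 37, alpha 0.05 (two-sided assumed).

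- SE = 37 × √(2/200) = 3.70.
- Power = Φ(13/3.70 − 1.96) = Φ(1.55) = 94.0%, against 90% stated.
- 90% power needs 171 per arm, or 171/0.8 → 214 per arm after loss, 428 in total against 500.

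The stated figure is not reproduced, but the gap is on the safe side. This point does not depend on it.

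**4. Size of the shift from the AE/SAE rule.** Assumptions, because the documents give neither quantity: a share f of CHANGE men with data is excluded, and their mean PDA lies g points below the arm mean. There is no true effect.

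- Shift: b = f × g / (1 − f)
- SE = 37 × √(1/200 + 1/[200(1 − f)])
- Two-sided false-positive rate = 1 − Φ(1.96 − b/SE) + Φ(−1.96 − b/SE)

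| f | g | b (points) | SE | False-positive rate | b as share of 13 |
|---|---|---|---|---|---|
| 2% (4 of 200) | 25 | 0.02×25/0.98 = 0.51 | 3.72 | 5.2% | 4% |
| 5% (10 of 200) | 25 | 0.05×25/0.95 = 1.32 | 3.75 | 6.4% | 10% |
| 10% (20 of 200) | 25 | 0.10×25/0.90 = 2.78 | 3.80 | 11.3% | 21% |

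Varying g from 15 to 35 gives 0.3–0.7 points (5.1–5.4%) at f = 2%, 0.8–1.8 points (5.5–7.8%) at 5%, and 1.7–3.9 points (7.2–17.6%) at 10%. Power is not the issue: with 10% of CHANGE removed, power for 13 points is still about 93%.

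**5. CETA rule.** The net shift in CHANGE minus EUC is f_C×g/(1−f_C) − f_E×g/(1−f_E). Assume 2% excluded in CHANGE and 5% in EUC. If CETA users average 15 points below their arm, the shift is 0.31 − 0.79 = −0.48; if 15 points above, it is +0.48. The sign depends entirely on the assumptions.

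**The case against.** The strongest reply is that few men may be affected and that the link to PDA is loose.

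- Referral is not automatic. {11b} makes it depend on the judgement of the research director and team, and suicidal ideation leads to referral or withdrawal only at imminent risk.
- Several triggers, such as medical admission, victimisation or lack of food, have no evident link to drinking.
- PDA covers 14 days at the 3-month assessment, whereas sessions run over 6 weeks, so intoxication at a session falls outside the outcome window.
- Adjustment for baseline PDA may absorb part of any prognostic difference.

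All of this stands as a reason to call the direction probable and the size unknown. It does not remove the contradiction or the one-arm rule, and baseline adjustment does not cover deterioration that begins later.

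A reader might infer three stronger things that the documents do not support:

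- **That every deteriorating or referred man is removed.** Referral is conditional, and partner-violence referrals are exempt.
- **That the CETA rule also favours CHANGE.** It applies to both arms. If EUC men seek CETA more often and are worse off, removing them works against CHANGE.
- **That the arm-specific rule must unmask the trial statistician.** The data manager and field team lead are already unmasked ({17a}) and could apply it.

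**Conclusion.** The contradiction is established from the text. The primary analysis is declared intention-to-treat, while {22}, {11b} and {30} remove randomised men for events after randomisation. The AE/SAE rule is asymmetric between arms and probably favours CHANGE, for drinking and for distress. The CETA rule is a separate departure with unknown direction.

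The size cannot be derived from the documents. Under the stated assumptions the AE/SAE shift is negligible at 2% excluded, modest at 5%, and about a fifth of the target difference at 10%, where the false-positive rate roughly doubles. The case for changing the plan does not rest on the higher figures: a one-arm, outcome-related exclusion should not be part of a primary comparison, and removing it is cheap.

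**What to change.** 1. Delete the sentences in {22} and {30} that exclude data from the analysis.
2. Reword {11b} so that referral does not end outcome data collection, and reconcile {11b} with both statements in {22} on events found at 3 months.
3. Seek the 3-month outcome for every randomised man and analyse him in his allocated arm, whatever AE, SAE, referral or CETA use occurs.
4. Recruitment began in September 2024, so some men may already have been withdrawn. Retain the data already collected from them, and treat outcomes that cannot be recovered as missing data under the primary analysis.
5. If exclusion of referred men or CETA users is of interest, keep it as a labelled sensitivity analysis applied identically in both arms. This also brings {30} into line with {11d}.

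Referral and care rules are unchanged. The cost is wording in the protocol and analysis plan, a few extra 3-month calls, and possibly a smaller effect estimate. There is time to do it: recruitment is expected to finish in 2026, and the analysis plan is to be approved before unmasking.

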**Methods:**

This study is a parallel-arm, single-blind, individually randomised controlled trial across Ukraine government-controlled territories. Following informed consent, we will recruit 500 adult war-affected men, randomised 1:1 to EUC and CHANGE, or EUC alone. Inclusion criteria include elevated levels of alcohol use (between 8 and 19, inclusive, on the Alcohol Use Disorder Identification Test); psychological distress (≥ 16 on the Kessler Psychological Distress Scale) and ability to speak Ukrainian or Russian. CHANGE will be delivered over 6 weeks by 14 community-based facilitators, with outcomes assessed at 3 months post-randomisation. The primary outcome for CHANGE is the PDA from alcohol at 3 months, measured using the Timeline Follow Back. Secondary outcomes include percentage days of heavy drinking, alcohol misuse, psychological distress (depression, anxiety, and posttraumatic stress disorder), functional disability, intimate partner violence perpetration and health economics indicators at 3 months. The primary analysis will follow an intention-to-treat approach. A mixed-methods process evaluation will examine facilitator competency, recruitment, retention/completion, appropriateness, dose received, fidelity and feasibility of delivery and acceptability.

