### Eligibility criteria {10}

Study participant inclusion criteria are Ukrainian adult men (age ≥ 18 years) residing in a territory controlled by the Ukrainian government with (i) a score between 8 and 19 (inclusive) on the Alcohol Use Disorder Identification Test (AUDIT) [26], indicating alcohol misuse; and (ii) a score equal to or greater than 16 on the Kessler Psychological Distress Scale (K10) [27], indicating high levels of psychological distress. Finally, participants must be able to speak Ukrainian and/or Russian spoken in Ukraine.

Exclusion criteria are (i) men with severe AUD (AUDIT score ≥ 20) or non-hazardous alcohol consumption (AUDIT < 8 [26]; (ii) men identified as being at imminent risk of suicide or other life-threatening risk (determined through three brief questions: ‘In the last month, have you had thoughts about suicide (or harming another person) or a suicide plan (or a plan to harm another person)?’; ‘Do you have ways to carry out this plan?’; and ‘Have you tried to kill yourself (or to kill or harm another person) in the past month?’); (iii) men who express high levels of homicidal ideation (determined by the person having thoughts, plans, ways to carry out the plan and/or experience in harming another person). These individuals will be offered a referral to a psychiatrist; (iv) men identified as having signs of severe mental disorders such as psychosis and/or severe cognitive impairment, assessed through a checklist of observable signs (e.g. not understanding questions, presenting confused speech, or limited communication skills); (v) men who have received other formalized brief psychological interventions (e.g. PM + , Common Elements Treatment Approach (CETA)) in the last year, as well as those who have received treatment for substance misuse (e.g. Alcoholics Anonymous, detoxification, replacement therapy programs) at any point in their lifetime; and (vi) men who are actively involved in military action and those who reside outside of Ukraine will also be excluded. Outcome assessors will carry out the screening procedures and will be trained on providing support for referral pathways to specialised care.

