### Outcomes {12}

The outcome assessors will conduct online data collection using tablets and the electronic data capture system ‘Open Data Kit’ (ODK, https://getodk.org) in a remote format (online, via Zoom, Google Meets, Viber, Telegram, other platforms or via the telephone). Outcome assessment takes approximately 2 h. The outcome assessors, EUC specialists and phone operators each received a separate 3-day online training. During the training, outcome assessors focused on using the outcome measures in ODK, general interviewing skills (including role play exercises), learnt about standard operating procedures, and safety procedures. Two of the outcome assessors were previously involved in the feasibility trial for CHANGE. The EUC specialists and telephone operators each received training in their own SOPs and research ethics. All data collectors receive regular supervision from the field team lead, and none are involved in delivering the intervention.

Outcome assessments will take place during baseline, and 3-months post-randomisation. Similar to the trial in Uganda [23], the primary outcome is the percentage of days abstinent (PDA) at the 3 months’ outcome assessment, adjusted for baseline PDA. Secondary outcomes will include the 3-months assessment in percentage days of heavy drinking, alcohol misuse, psychological distress, depression, anxiety, PTSD, functional disability and perpetration of intimate partner violence. Additionally, quality of life, subjective wellbeing and capabilities-based wellbeing will be measured as secondary outcomes. The outcomes of the trial are summarised in Table 2, with a description of the assessment measures of the outcomes in Table 3. Furthermore, sociodemographic data will be collected during the baseline assessment including level of education, socio-economic status, data on whether they have been displaced and their involvement in military action. At follow-up, we will also collect data on socio-economic status to identify changes. A contamination measure will be used at the 3-month follow up to measure potential contamination of intervention strategies between the two intervention arms. Table 4 describes the socio-demographic data collected at baseline, and Fig. 1 provides an overview of the planned enrolment, allocation, intervention delivery and outcome assessments.

**Table 2 Tab2:** Primary and secondary outcomes of the trial (table adapted from Van Der Boor et al., 2024 [23])

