United Nations Multi Country Study on Men and Violence	Eleven items are used to measure the prevalence of perpetration of violence in the last 3 months. The items are assessed on a scale of 1 to 4, or 1 to 7	Prevalence of IPV split by type of intimate partner violence (physical, sexual)	Previously validated in Bangladesh, China, Cambodia, Indonesia, Sri Lanka, and Papua New Guinea [34]
EQ-5D-L	Five item questionnaire for measuring health related quality of life across five dimensions: mobility, self-care, usual activities, pain/discomfort, and anxiety/depression, rated on the day. A five-level response option is used	Locally adjusted scoring algorithm	Validated across different contexts including Ukraine (https://euroqol.org/register/obtain-eq-5d/available-versions/)
Subjective Wellbeing	Five items on subjective wellbeing, measuring overall life satisfaction, whether the things the respondent does are worthwhile, and affect; scored on a scale of 1 to 5	Locally adjusted scoring algorithm	Used across countries in the Gallup world poll which covers more than 150 countries, including Ukraine (https://www.gallup.com/analytics/349487/world-happiness-report.aspx)
OxCAP-MH	Sixteen item index on wellbeing, covering various domains of individual well-being including overall health, enjoying social and recreational activities, friendship, and support, having suitable accommodation etc. Scored on a scale of 1 to 5	Mean score	Has been contextually translated and validated by the current research team in Ukraine into Ukrainian and Russian spoken in Ukraine (publication forthcoming)
User Cost Questionnaire	Fifteen item measure on household expenditure specifically designed for this trial to measure the opportunity cost of participating in the CHANGE intervention	The opportunity cost of participating in the CHANGE intervention	Specifically designed and piloted for this trial. Based on the iMTA productivity loss of cost questionnaire

**Table 4 Tab4:** Sociodemographic data collection

Construct	Measure
Education	Education (no school, primary, secondary, tertiary education, etc.)
Age	In years
Socio-economic status	Self-perceived relative socio-economic status (e.g., income level as multiple-choice question)
Trauma exposure	Life Events Checklist
Use of local substances (e.g., khat, tobacco, marijuana, opioids, synthetic drugs etc.)	Measured developed for study or standardized measure (e.g., ASSIST)
Displacement status	Multiple-choice answer

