Following the baseline assessment, an EUC specialist will join the call or set up a separate call with participant (on a separate day) to go through an electronic information pamphlet (detailing information on reducing alcohol intake and managing psychological distress as well as outlining ways of contacting alternative psychological services). The EUC specialist will also carry out the randomisation procedure, as detailed in the section below. Those randomised to the intervention arm will receive their first CHANGE session the week after (see Fig. 1).

Participants will be followed up at 3-months after baseline for the outcome assessment. Additional qualitative interviews will be carried out at 3 months follow-up using a purposive sampling strategy. Qualitative interviews will be carried out with all intervention facilitators ( *N* = 14), supervisors (*N* = 4), outcome assessors (*N* = 2) and phone operators (*N* = 2), in addition to family members of participants (*N* = 20), participants in the intervention arm (*N* = 20), participants in the control arm (*N* = 20) and as many participants who dropped out as possible (Fig. 2).

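### The safety questions repeated at 3 months look back one month, so suicidality and non-partner harm in roughly the first two months are not asked about alike in both arms

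*Protocol article*

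**What the plan says.** The protocol article prints three safety questions under Eligibility criteria {10}:

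- Thoughts and plans: "In the last month, have you had thoughts about suicide (or harming another person) or a suicide plan".
- Means: "Do you have ways to carry out this plan". This has no time window of its own and depends on the first question.
- Attempts and harm to others: "Have you tried to kill yourself (or to kill or harm another person) in the past month".

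Under Adverse event reporting and harms {22}, at the 3-month follow-up, "all participants will be asked to respond to the safety questions (related to suicide and homicidal ideation) again". No changed recall period is given there. The same paragraph links a detected serious adverse event (SAE) to a psychiatric assessment and an SAE report, and gives the questions the aim of finding problems and arranging referral.

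On timing, Outcomes {12} states: "Outcome assessments will take place during baseline, and 3-months post-randomisation". The abstract states: "CHANGE will be delivered over 6 weeks by 14 community-based facilitators, with outcomes assessed at 3 months post-randomisation". Participant timeline {13} adds: "Those randomised to the intervention arm will receive their first CHANGE session the week after".

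On other routes, section {22} sets up a critical incident register for events found at outcome assessments or in intervention sessions. Table 6 has one column for reports at outcome evaluation in both arms and another for reports by facilitators, in the intervention arm only. For the partner-violence instrument, Table 3 states: "Eleven items are used to measure the prevalence of perpetration of violence in the last 3 months".

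**The concern.** The questions were written to decide eligibility on the day of screening. A one-month look-back suits that use, but repeated at a 3-month visit it does not reach back to randomisation. A man in the EUC arm who attempted suicide in week 5 and is asked in week 13 can truthfully answer no.

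Suicide attempt is listed as an SAE in Table 5, and SAEs go to the DSMB. A comparison of such events by arm needs both arms to be asked the same question over the same period. Here the one shared enquiry covers the last month, while the route that operates in the earlier weeks, the facilitator sessions, exists only for men allocated to CHANGE. If the true rates were equal, this would tend to show more recorded events in the CHANGE arm simply because someone was there to hear of them.

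**Working it through.** The plan gives no computed figure on this point, so there is nothing to reproduce. The check uses the stated windows and visit times.

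**Step 1: the window.** One month = 365.25 / 12 = 30.4 days. The follow-up visit is at 3 × 30.44 = 91.3 days. The window opens at 91.3 − 30.4 = day 60.9. Share of follow-up before it opens: 60.9 / 91.3 = 66.7%.

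**Step 2: the CHANGE sessions.** Six weekly sessions begin the week after randomisation, so I take the first on day 7 to 14. Session 6 is then on day 7 + 35 = 42 to 14 + 35 = 49. It precedes the window by 60.9 − 42 = 18.9 days to 60.9 − 49 = 11.9 days. An optional booster is allowed, with no stated timing. If it came one week after session 6, it would fall on day 49 to 56, still 11.9 to 4.9 days before the window. On schedule, no session falls inside the window. A slip of more than about 12 to 19 days would bring session 6 into it.

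**Step 3: what is stated for an event in about days 0 to 61.**

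| Event | EUC alone | CHANGE plus EUC |
|---|---|---|
| Suicidal thoughts, plan or attempt | Recorded if it comes up at 3 months; no stated question covers the period | The same, plus the sessions |
| Harm to someone other than a partner | Recorded if it comes up at 3 months; no stated question covers the period | The same, plus the sessions |
| Physical or sexual violence against a partner | Asked at 3 months over the last 3 months | The same, plus the sessions |

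The first two rows are the gap. The third is covered in both arms.

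**Step 4: illustration of size.** The documents give no event rate. Assume a constant hazard and a 3-month risk r of 1%, 2% or 5% among 500 men. Men with an event over 3 months = 500 × r. Men with an event inside the last-month window = 500 × [1 − (1 − r)^(1/3)].

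- r = 1%: 1.7 of 5
- r = 2%: 3.4 of 10
- r = 5%: 8.5 of 25

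These are the men whom the past-month questions could find. They are not the total that the trial would record, because other routes exist.

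**Step 5: after the change.** A look-back to baseline covers the whole 91 days, so coverage rises from one third to all of follow-up.

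**The case against.** The strongest reply is that the repeated questions are not meant to count events. Section {22} describes them as a way to find problems and refer men promptly, and a one-month look-back suits that use. This stands, and it is a reason to leave those items as they are. It does not close the gap, because the same paragraph ties the questions to SAE detection and no other enquiry about suicidality in both arms is stated.

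A second reply is that SAE recording is wider than three questions. Table 6 expects reports at outcome evaluation in both arms of events such as hospital admission, victimisation and suicide attempt, and sets no one-month limit. Section {22} also plans regular check-ins for high-risk cases. This stands too. A reader might infer that everything in the first two months goes unrecorded, or that two thirds of attempts are lost. The documents do not support either: events can be volunteered at 3 months or raised in sessions and then registered. What they do not show is how such events are elicited, and the check-ins reach only men already identified as at risk.

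Third, a reader might infer that all harm to others is missed. That is wrong for partner violence, which both arms are asked about over 3 months.

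Fourth, the follow-up wording is inferred from the word *again*. The article condenses a fuller protocol, and the electronic form is not shown. This lowers confidence. The point still rests on what is printed, which is a fixed wording and its reuse.

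Fifth, the claim that no session falls inside the window depends on the schedule. Air-raid interruptions, power cuts and missed sessions are all foreseen in the article, so some men will have sessions within it.

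**Conclusion.** The point holds in a limited form, with moderate confidence. On the natural reading, suicidal thoughts, plans and attempts, and harm to people other than a partner, are not covered by any stated systematic enquiry in both arms for about the first 61 of 91 days, or 67% of follow-up. That period includes the CHANGE sessions if they run to schedule. Because the session route serves one arm only, counts of suicide attempts and non-partner violence would be incomplete and not comparable between arms.

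The 67% depends only on the two stated time spans. The illustrative event counts also need the assumed risks and a constant hazard, and are not estimates for this trial. How far recorded SAEs would fall short cannot be worked out from the documents, since the yield of volunteered reports and of sessions is unknown. If the follow-up form already asks about the time since baseline, one sentence in the protocol resolves the point.

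**What to change.** At the 3-month visit, keep the past-month items unchanged for current risk and referral. Add, in both arms, the same two or three items with recall since the baseline assessment, and ask for the approximate date of any event. Report suicide attempts and non-partner violence by arm from the added items, and list separately the events that were detected only in CHANGE sessions. Start the new items on one calendar date in both arms, and state how many men in each arm answered them.

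The cost is a small change to the electronic form, an ethics notification and about one minute in an assessment of about 2 hours, with no new visit or staff. Recall over 3 months is less precise than over one month, although the partner-violence items at the same visit already rely on it. Recruitment began in September 2024, so men already followed up would not be covered. With recruitment expected to finish in 2026, later participants still could be.
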